## Abstract

**Background:**

Mental health is a global issue requiring global attention. Depression and anxiety are two of the most common mental disorders (CMDs) and are characterized by high incidence and high comorbidity. In recent years, the prolonged COVID-19 pandemic and exacerbated social instability have posed significant challenges to the mental resilience and mental health outcomes of the global population. Now more than ever, with an increase in mental health needs, it has become even more crucial to find an effective solution to provide universal mental healthcare. Psychotherapy is of vital importance for those coping with symptoms of depression and anxiety and is used to enhance mental resilience. However, such therapy can be difficult to access in reality. In this context, the *Micro-Video Psychological Training Camp (MVPTC)* platform will be developed.

**Objectives:**

As an online self-help platform for psychological intervention, the *MVPTC* platform was developed for those who suffer from mild to moderate symptoms of depression and/or anxiety and is tasked with the goal of reducing depressive and anxious symptoms while improving mental resilience. Thus, this study will be carried out to verify its efficacy and applicability.

**Methods:**

In this parallel-group, randomized controlled trial, a total of 200 mild to moderately depressed and/or anxious adults seeking self-help will be randomly recruited and assigned to either the micro-video psychological intervention group or the wait list control group. Online measurements by self-assessment will be taken at baseline, post-intervention, 1-month, and 3-month follow-up.

**Results:**

The primary results will involve symptoms of depression and anxiety. The secondary results will involve mental resilience. An analysis will be conducted based on the intention-to-treat principle.

**Discussion:**

This trial will examine whether the *MVPTC* platform for the relief of symptoms and the enhancement of resilience in a population screened for depression and anxiety symptoms proves effective and applicable. Large-scale resilience enhancement may benefit public mental health in terms of preventive interventions, managing depressive and anxiety symptoms, and promoting mental health. With the *MVPTC*-based method being applied, a brief, efficient, and structured intervention model can potentially be established, having the potential to provide necessary and accessible mental support for an extensive target group.

**Clinical trial registration:**

http://www.chictr.org.cn/, identifier ChiCTR2100043725.

## 1. Introduction

### 1.1. Background

Mental health is a global issue requiring global attention. Depression and anxiety disorder, the two main diagnostic categories of common mental disorder (CMD), are prevalent in many populations, with symptoms ranging from mild to severe. According to estimates, there are over 300 million people (making up 4.4% of the global population) who suffer from depression, and over 264 million people (equivalent to 3.6% of the world’s population) who are affected by an anxiety disorder, with a large proportion of the world’s population suffering from both (comorbidity) (1). Social functioning and quality of life may be affected to varying degrees from the onset of prodromal symptoms to a definite diagnosis (2–4), concomitant with personal stress, and social burden. China is one of the countries with the highest burden of depression and anxiety in the world (5).

To some extent, depression and anxiety are considered stressor-related diseases (6). In low- and middle-income countries (LMICs), people can be more easily affected by various stressors, making them more vulnerable to developing psychological symptoms and/or mental disorders, including depression and anxiety (7, 8). In terms of defining psychological resilience, this refers to the capacity of individuals to cope with challenges or stress while maintaining mental health despite exposure to a myriad of adversity in life (6, 9). Resilience can also be considered a significant factor in protecting people from developing symptoms of mental disorders in emergency situations (2, 10). Meanwhile, studies have also shown that resilience interventions can improve depressive symptoms in patients with depression (11). It can be seen that resilience intervention plays a key role in the development of depression and anxiety symptoms, from the prodromal stage with subclinical symptoms to moderate mental distress in patients with a definite diagnosis.

In recent years, the prolonged COVID-19 pandemic and waning economies, which have aggravated short- and long-term stresses and increased social instability, have posed significant challenges to the mental resilience and mental health outcomes of the global population, especially for susceptible groups of the population (12). Some studies report that the number of people with depression and anxiety is on the rise (13).

As an effective and evidence-based treatment protocol, psychotherapy is of great importance in the management of anxiety and depression (14) and is also a factor that can enhance resilience, as suggested by previous studies. Enhanced self-esteem and increased self-efficacy, emotional regulation, meaning-making, flexible coping capacity, and better interpersonal relationships are the main preventative factors associated with resilience. All of this can be improved by psychological intervention (15), thereby relieving the symptoms of mental disorders and improving mental health (11, 16).

Some effective evidence-based therapies currently exist, but they are not easily accessible, much less in terms of access to standard and effective treatment procedures. Larger populations have a greater need for mental health services, but the real number of patients who can access effective interventions remains limited in number (7, 8). Studies have suggested that over 70% of patients with depression do not seek treatment (17, 18). In fact, among the group of patients who have received psychotherapy, only 27% of them received standardized treatments (19). The demand for interventions involving mental health among patients is low and is the result of various obstacles of differing degrees. Apart from geographic distance and outbreak isolation, the stigma attached to mental disorders remains one of the more prominent obstacles (20). Even when patients are ready to seek treatment, they may still encounter difficulties, such as a shortage of reliable and quality services, a limited number of qualified and professional service providers, and prolonged wait times, as these commonly occur in underdeveloped or isolated areas (21, 22).

Now more than ever, with an increase in mental health needs, it becomes even more vital to find an effective solution that can afford people universal mental healthcare (4). Therefore, a therapeutic tool combining new Internet technology and psychological intervention [e.g., Internet-Based Cognitive Behavior Therapy (iCBT) and Computerized Cognitive Behavior Therapy (cCBT)] will be developed to effectively address this issue. Some studies have reported that digital self-service psychological intervention has an active treatment effect on depression (23, 24) as well as anxiety disorders (25–27). As one of the earliest groups studying intelligent psychological intervention in China, our team already has a foundation in computerized cognitive behavioral therapy for obsessive-compulsive disorder and substance-use disorders (28–30) and has developed an artificial intelligence (AI)-based psychological Chatbot app to help with anxiety disorders.

In this study, the *Micro-Video Psychological Training Camp (MVPTC)*, a self-service online psychological intervention platform, will be developed and aims to be more accessible to a larger number of people. This intervention method, as a supplement to existing psychotherapy resources, can monitor mood, improve mental resilience, and provide psychotherapy based on cognitive behavior therapy (CBT), incorporating core techniques and principles of other psychological therapy methods. For participants with mild to moderate depression and/or anxiety with no immediate risk, treatment indication can be used to alleviate disease symptoms. Furthermore, as an indicated prevention or early treatment intervention, this method has the potential to reduce the risk of disease in the future among ordinary people or high-risk groups, realizing preventive intervention for more vulnerable groups (4).

### 1.2. Objectives

In this study, a prospective, parallel-group, randomized controlled clinical trial will be conducted to probe the applicability and efficacy of *MVPTC* on alleviating symptoms and improving mental resilience in participants with mild to moderate depression and/or anxiety.

Specifically, this trial will be designed to see if the symptoms of depression and/or anxiety are significantly reduced and mental resilience is significantly improved in the micro-video psychological intervention group when compared with the wait list control group.

## 2. Methods

### 2.1. Trial design

This will be a single-center, parallel-group, randomized controlled trial. A total of 200 participants will be randomly chosen and equally divided into the micro-video psychological intervention group and the wait list control group based on a randomly generated table of numbers with 100 participants in each group. The self-service psychological intervention group will be the testing group, and the wait list control group will be the control group.

### 2.2. Setting and recruitment

Mild to moderately depressed and anxious adults seeking self-help will be recruited from the psychological clinic of the SMHC, the community, and the Internet. Those who will be involved in recruitment and administration, i.e., the referring doctor (outpatient psychiatrists in SMHC), community staff (psychiatrists in the community center), and mailbox manager (psychotherapists certified by the National Health Commission), are all familiar with our study. They will conduct an initial face-to-face or telephone screening for about 15 min and then recommend suitable participants to our trained researchers. Next, our researchers will make a detailed introduction to these participants and extend a participation invitation for the trial. Before conducting the screening visit, voluntary participants in the trial will sign the electronicinformed consent forms (ICFs). During the screening visit, we used the Self-Rating Depression Scale (SDS) and the Self-Rating Anxiety Scale (SAS) scales as a criterion for inclusion access and the Mini International Neuropsychiatry Interview (MINI 6.0.0) as a diagnostic assessment to exclude other psychiatric disorders that interfered with the study. Moreover, significant suicidal ideation was included in the screening visit (i.e., they had active thoughts, plans, or behaviors of self-injury or suicide in recent months or in the past). Other criteria are listed in the “participants and eligibility” section. Participants who meet the criteria will be able to proceed to the next stage. The specific flowchart is found in Figure 1.

**FIGURE 1 F1:**
[figure not shown]
Study design and measurement time points. SDS, The Self-Rating Depression Scale; SAS, The Self-Rating Anxiety Scale; CD-RISC, The Connor-Davidson Resilience Scale; ISI, Insomnia Severity Index; PSSS, Perceived Social Support Scale; SASE, Self-Assessment Scale of the Overall Efficacy and Satisfaction of Participants.

### 2.3. Participants and eligibility

Participants will be included in this study if (1) they are 18–55 years of age; (2) they have mild to moderate depressive symptoms with a score between 53 and 72 on the SDS, mild to moderate symptoms of anxiety with a score between 50 and 69 on the SAS, or both; (3) they have a junior/middle school education or above and are good with using a smartphone; (4) they have not received psychiatric medication; (5) they have not received systematic psychotherapy within the past 6 months but are relatively motivated to receive treatment; and (6) they volunteered to participate and signed the ICF after fully understanding all aspects of the trial.

Participants will be excluded from the study if they meet the following criteria. (1) They have an onset of a concurrent severe physical disease that is not well controlled or if any existing physical disease that requires priority for physical treatment is exacerbated. (2) They have an immediate risk or medical treatment indication, such as depressive symptoms or anxiety symptoms that exceed the threshold limit or significant suicidal ideation reflected on the initial screening visit and scale (initial SDS item 20 score > 1). Those who fail to meet the selection criteria will be notified and advised to seek the help of a psychiatrist at an outpatient clinic. In cases of intense suicidal ideation, people will be urgently referred to a psychiatrist for a higher level and more urgent treatment. (3) They suffer a lifetime DSM-5 psychiatric disorder, other than depression and anxiety disorder, which includes psychotic symptoms, neurological disease, substance abuse, personality disorder, and mental retardation. (4) They have participated in other clinical studies.

### 2.4. Randomization

Randomization of the trial will be based on a computer-generated randomization list. After returning their ICF and completing the baseline questionnaire, people who meet the inclusion criteria will be randomly allocated to the *MVPTC* intervention group or to the waiting list control group and then will receive a notification *via* WeChat message. Later, a computer program will allocate participants using a generated randomization list. Block randomization in blocks of two will be used to ensure an equal distribution of participants across conditions.

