On WeChat, the most frequently used app in China, the *MVPTC* applet platform is easily accessible to users. Participants can use the platform conveniently in the privacy of their own homes, with more flexibility, and in a relatively anonymous way. Mandatory hospital or treatment room visitations can be reduced after using this platform, and it brings a lot of convenience for participants even in this pandemic era, no matter where they are. This can save transportation time and streamline the treatment process. In addition, the platform’s online application can reduce the time spent with clinicians while minimizing costs, which can make intervention treatment accessible to more populations.

By using the management system of the applet, all participants can be monitored and tracked by the researchers. While the platform does not have a crisis management function, when participants in both groups face the risk of self-injury, suicide, or exacerbating their symptoms of depression and anxiety, researchers still have the option of halting the study after discussed with the research team. Furthermore, participants in this situation can be recommended by researchers to receive emergency medical treatment. If necessary, the participant’s guardian or family member can be contacted to talk about the possible need for higher-level treatment, such as medication or hospitalization. All of this will be informed consent at the beginning of the study.

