## 3. Outcome measurements and instruments

The study assessment will be completed online by the subjects on a self-help basis. Self-rating scales were used in this study. The analysis of these scales will be conducted by a statistician without knowing how the subjects are allocated.

The efficacy indicators include (1) the primary outcome: the change in the SDS score and the SAS score between groups at different times. In particular, if the reduction rate is ≥50%, an obvious effect will be shown; if the rate is <50 and ≥25%, the effect is only average; and if the rate is <25%, no clinical effect will exist. (2) The secondary efficacy outcome is based on The Connor-Davidson Resilience Scale (CD-RISC) score, which can be increased as symptoms of anxiety and depression improve during the treatment process. In addition, measurements including the Insomnia Severity Index (ISI) and the Perceived Social Support Scale (PSSS) will be provided.

The applicability indicators include the intervention completion rate, the dropping rate, and the Self-Assessment Scale of the Overall Efficacy and Satisfaction of Participants (SASE) score.

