## 5. Discussion

This online trial will examine whether a self-help psychological intervention platform that helps alleviate depression and/or anxiety symptoms and enhance resilience will be effective in terms of clinical outcomes and applicability.

This study has several inherent limitations. First, there may be dropouts in either of the two groups. We will conduct a dropout analysis and a survey to examine the reasons why the dropouts withdrew from the study. Second, since we will only use self-report questionnaires instead of examiner-rating scales or formal diagnostic instruments, there may be a bias resulting from the participants knowing their group. In addition, the elderly and participants with severe symptoms may have some inconvenience when using their mobile phones for online measurement. We opted for self-rating because, theoretically, the measurement and intervention should be easily accessible and highly applicable. Third, we anticipate that younger people, more psychologically engaged individuals, or more motivated people will be attracted by this open recruitment strategy. Accordingly, we should be cautious when generalizing results about a certain type of population. Finally, using a waiting list trial design poses substantial limitations on the validity and universality of the results. Mild to moderate depression and anxiety symptoms have a tendency to heal on their own, and there is also a probability that the control group will also take various self-help measures, which would underestimate the intervention effect of our study.

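### Fixed blocks of two make the second allocation of each pair inferable, and the protocol does not say that recruiting staff are shielded from earlier assignments

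*Protocol article*

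**What the plan says.** All references are to the protocol article.

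- **Block size.** Section 2.4 states: "Block randomization in blocks of two will be used to ensure an equal distribution of participants across conditions". It names no second or varying size and no stratification factor.
- **Mechanism and timing.** Section 2.4 also says: "Later, a computer program will allocate participants using a generated randomization list". Allocation follows consent and baseline assessment ("After returning their ICF and completing the baseline questionnaire, people who meet the inclusion criteria will be randomly allocated to the" one of the two groups), and the participant is then told the result by WeChat.
- **Sites and size.** Section 2.1: "This will be a single-center, parallel-group, randomized controlled trial". The 200 participants are split equally, "based on a randomly generated table of numbers with 100 participants in each group".
- **Blinding.** Section 3: "The analysis of these scales will be conducted by a statistician without knowing how the subjects are allocated". No other role is said to be blind. Section 5 accepts that "there may be a bias resulting from the participants knowing their group".
- **Sight of participants after allocation.** Section 2.5.3.1: "By using the management system of the applet, all participants can be monitored and tracked by the researchers".
- **Entry.** Under section 2.2, referring doctors, community staff and a mailbox manager do a short first screen and pass suitable people to the study's researchers, who invite them.

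**The concern.** Concealment has two parts: nobody can look up the next assignment, and nobody can work it out. A computer program holding the list takes care of the first. It does nothing for the second if the pattern is so short that the last assignment reveals the next. Two is the smallest possible 1:1 block, so it is the most predictable permuted-block scheme.

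The setting gives little protection against someone learning the last assignment. One arm uses an applet and the other waits, so the arm shows in ordinary trial conduct. Researchers can follow everyone in the management system, and the block size is in print.

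If staff who influence entry can tell which arm comes next, they may consciously or not bring forward or delay a candidate. Section 2.3 requires candidates to be relatively motivated, which leaves some judgement. Motivation plausibly affects adherence and self-rated outcome. The primary outcomes, SDS and SAS, are both self-rated, so no blinded assessor stands between such selection and the result. Selection on unmeasured prognosis cannot be undone in the analysis once enrolment is complete.

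**Working it through.** **Inputs.** Block size 2 (section 2.4); 200 participants, 1:1, one center (section 2.1); for the illustration only, SDS standard deviation 8 (Table 2, section 2.7).

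**1. The plan's own figure.** 200 / 2 = 100 blocks, each placing one participant in each arm, gives 100 per arm. The stated split is reproduced.

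**2. Allocations that are certain.** For a permuted block of size b = 2h, the expected share of allocations fully determined by earlier ones in the block is 1/(h + 1). For b = 2 this is 1/2, that is 100 of 200.

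**3. Best-guess success.** Someone who knows the block size and the past assignments, and always guesses the arm that is behind, is right on average h + (4^h / C(2h, h) − 1)/2 times per block. For b = 2: 1 + (4/2 − 1)/2 = 1.5 of 2, or 75% (150 of 200).

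**4. Comparison.** Exact enumeration gives the same results as these formulas.

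| Scheme | Certain | Best guess correct |
|---|---|---|
| Fixed 2 (plan) | 50% (100) | 75.0% |
| Fixed 4 | 33.3% (about 67) | 70.8% |
| Fixed 6 | 25.0% (50) | 68.3% |
| Fixed 8 | 20.0% (40) | 66.6% |
| Random mix of 4, 6, 8, order unknown | almost none | about 68% |
| Simple randomization | 0% | 50% |

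The best-guess figure for the mix comes from 4,000 simulated lists of 200, guessing the arm currently behind. A separate check of the word *almost* used 3,000 simulated lists and an observer who knows that the sizes are 4, 6 and 8 in equal proportions but not their order. About 2% of allocations were then certain.

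**5. Cost in balance.** A list cut off at 200 can stop inside a block of 8. The worst case is the first four all in one arm, an imbalance of 4.

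**6. What selection could do (illustration; the shift d is an assumption).** Suppose selection moves the expected SDS outcome by d points in favour of the intervention on each certain allocation. Of the 100 certain allocations, 50 fall in each arm, half of that arm. Each arm mean moves by d/2 in opposite directions, so the group difference is biased by d. The standard error is 8 × √(2/100) = 1.13. The two-sided type I error is P(Z > 1.96 − d/1.13) + P(Z < −1.96 − d/1.13):

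- d = 0.5: about 7%
- d = 1: about 14%
- d = 2: about 42%

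The documents give no value for d, and d = 0 is possible.

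**The case against.** The best counter-argument is that inferable is not the same as known. Foreknowledge needs three things together: the block size, the previous assignment and the next candidate's place in the order. Section 2.4 has a program allocate and the participant receive the message; it does not say that recruiters see the result. Candidates come from the clinic, the community and the Internet, and complete consent and baseline online. Their own timing therefore partly sets the order, and parallel enrolment blurs who is next. Core eligibility is numeric (SDS, SAS and SDS item 20) plus a structured interview, which narrows discretion. Custody of the list and separation of roles may be described in the full protocol, which is not shown.

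Much of this stands, and it rules out several stronger readings that a reader might infer:

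- *Recruiters know every second allocation, so allocation is not concealed.* The text does not show that they see earlier assignments, and the first of each pair is unpredictable in any case.
- *The staff who invite are the staff who monitor.* Sections 2.2 and 2.5.3.1 both speak of researchers, but do not say that they are the same individuals or that the system shows the order of allocation.
- *Candidates could be screened again to obtain a preferred arm.* No such procedure is described.
- *Any selection passes straight into the primary comparison.* The primary outcome is change in score, and section 4 analyses group by time, so selection on baseline severity does not carry over one for one. Selection on motivation or prognosis could.

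What the objection does not remove is the stated rule itself. The block size is a fixed design choice, not a detail left out for brevity, and no section excludes the conditions under which it can be exploited.

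**Conclusion.** The point holds as a weakness in a stated rule. With fixed blocks of two, 100 of 200 allocations (50%) can be inferred, and 75% guessed, by anyone who has the block size, the previous assignment and the order of entry. These figures are exact under 1:1 allocation in a single unstratified sequence, which is what the article describes.

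That someone involved in recruitment has this information is an assumption. The visible difference between arms, the researchers' access to participant monitoring and the absence of any stated shielding make it plausible. Selection bias in the SDS and SAS comparison is therefore a credible risk of unknown size, not something the document shows to have happened. Because the rule is easily improved and its consequences cannot be repaired afterwards, it should be fixed; the evidence does not justify treating it as fatal.

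**What to change.** Replace the blocks of two in section 2.4 with permuted blocks of randomly varying larger size, for example 4, 6 and 8. Have the list generated by someone outside recruitment, and keep the sizes out of any document that recruiting staff see. If enrolment has started, apply this to all remaining allocations. Releasing the assignment only after consent and baseline is already the order given in section 2.4 and should be kept.

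The main gain is the loss of certainty: from half of all allocations to almost none. The gain in guessing is modest, from 75% to about 68%. The cost is one regenerated list, a sentence of protocol text and a final imbalance of at most 4 of 200 participants, which is negligible for comparing two groups of about 100.
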